## **9.3 Assessment of results- effectiveness parameters**

Blood samples, buccal swabs, salivary samples, fecal samples, and skin swabs are taken by clinical staff and stored in the neonatal unit until transported to the CMM/KI (epigenetics), Linköping University Hospital, The Center for Translational Microbiome Research/MTC (microbiota). This includes also samples taken in Stavanger. All samples are encompassed by existing biobank regulations in each country, and authorization has been given. Clinical data is collected from hospital case record. Information on attachment, parental health and part of psychomotor development is collected from case record, other part from questionnaires and films. MR data is analyzed by neuroradiology specialists at Karolinska University Hospital and Stavanger University Hospital. Many outcomes are of a nature that reference values and detection limits do not apply, rather evaluation is by association studies and exploratory analysis.

#### **9.4 Assessment of analysis results – safety parameters**

For all outcomes safety margins and intervals do not apply. Should any result be abnormal or indicate need for investigation or management, subject will be promptly referred.

## **10 MANAGEMENT OF ADVERSE EVENTS**

### **10.1 Definitions**

#### **10.1.1 Adverse event (AE)**

Every adverse clinical event or deterioration of existing medical condition, regardless of any connection to study intervention.

#### **10.1.2 Serious adverse event (SAE)**

Every unintended medical event that:

- Results in death
- Is life-threatening
- Leads to a prolonged hospital stay
- Results in permanent or temporary disability
- Leads to injury or deformity
- Is serious for any other reason

### **10.2 Evaluation of adverse events**

#### **10.2.1 Evaluation of severity**

Every adverse event shall be classified by the researcher as mild moderate or severe.

**Mild:** The event does not impact the subjects' normal life.

**Moderate:** The event causes deterioration in function but does not impact health. The event gives discomfort and or impediment.

**Severe:** The event leads to deterioration of function or work capacity or constitutes a health risk for the subject.

#### **10.2.2 Evaluation of association to intervention**

**Likely:** Clinical event, including abnormal laboratory results that occur within a plausible time after the intervention or study product. Unlikely that the event can be attributed to underlying medical conditions or pharmaceuticals.

**Possible:** Clinical event, including abnormal laboratory tests, that occurs within a reasonable time following the intervention or study product. The event can be attributed to underlying medical condition or to other drugs.

**Unlikely:** Clinical event, including abnormal laboratory tests, that could potentially be related to the intervention or study product. The event is unlikely to be related to the intervention or study product and can be explained by other drugs or by the underlying medical condition.

**Not possible to classify:** The event cannot be classified due to lack of information, or the event is not verified.

### 10.3 Methods to discover adverse events

Adverse events are:

- Death
- Cardiorespiratory deterioration with need for increased intensive care, for example apnea obs vi har ett stavfel högre upp with need for ventilation, circulatory collapse with need for bolus fluids and inotrope treatment. Acquired infections.
- Intraventricular haemorrhages
- Nil per mouth due to suspected necrotizing enterocolitis.
- Other conditions requiring transfer to higher level of care.

Of the above examples, death and any condition with risk of death and prolonged hospital care and future disability are categorized as severe adverse events.

A Data Safety Monitoring Board (DSMB) will oversee the study and its data independently. The DSMB will be chosen to include competence in neonatology, epidemiology, global health, and biostatistics. The DSMB will receive quarterly reports from a statistician on safety data. Based on this the DSMB can recommend pausing study enrollment, modify the study intervention or stop the study.

Investigator, co-investigators, and research nurses will within 24 hours report all serious adverse events to sponsor, and all adverse events on a monthly basis. The sponsor will inform the DSMB within one week of a serious event and collated every 6 months for adverse events.

An interim analysis is planned after 30 subjects have been enrolled.

### 10.4 Reporting of adverse events

#### 10.4.1 *Reporting of adverse events*

All adverse events shall be reported on provided report form in the CRF.

#### 10.4.2 *Reporting of serious adverse events*

Serious adverse events shall be reported to sponsor on assigned SAE form within 24 hours from researcher being aware of event. Complementary information that describes the outcome of the SAE and its ongoing management shall be reported as soon as available. The originals of these documents shall be filed in CRF and research folder.

### 10.5 Follow-up of adverse events

Since the intervention includes the first six hours of life, our study subjects will be receiving ongoing care then and for a considerable time thereafter. Adverse events are an expected part of care of preterm infants and will receive

the customary clinical care. Nevertheless, for all study subjects every adverse event and subsequent outcomes will be documented as described above.

## **11 STATISTICS AND DATA MANAGEMENT**

### **11.1 Data management**

Data will be collected manually on paper, using paper based CRF. At a later stage electronic CRF may be introduced. From these data will be fed into a database within one week, in English with translation from Swedish and Norwegian as required. In the CRF data will be anonymous, with a confidential study ID without sensitive personal identifiers. The study ID will be found in the hospital case record, as well as coded and kept securely with secure passwords. Investigator is responsible to ensure that the data entered into the CRF is correct and will attest in writing in each case.

Data to be entered into the CRF will be carefully defined before study launch, with a defined source code. All adverse events will be reported to sponsor and entered into CRF and database.

All handling of data will be according to the guidelines of Good Clinical Practice (GCP). Investigator is responsible for ensuring source data is accessible for monitoring.

All changes and corrections of the CRF must be dated, signed, and explained, and the originally entered data should be retained. When all data has been entered, verified, and validated it will be locked.

### **11.2 Statistiscal analysis**

Primary outcome analysis will be done according to intention to treat (ITT) on all subjects that met inclusion criteria without exclusion criteria and were randomized. Per protocol analysis will also be undertaken based on actual adherence to allocated place of care. For safety measures the entire sample will be included. All continuous variables will be described with sample size and number of observations, average and median values, with standard deviations and minimum and maximum values. All categorical variables will be summarized in frequency tables. For the primary outcome a mixed model-regression analysis will be done to evaluate the effect of gestational age, birth order, single or multiple birth, intrauterine growth retardation, mode of birth (vaginal or caesarean), antenatal corticosteroids given or not, and birth weight. The null hypothesis is that there is no difference in the groups for the primary outcome. The analysis will be done for the whole study population as well as those that received the intervention.

An interim analysis will be done for the primary outcome on the first 30 patients enrolled.

Secondary outcomes that are continuous or categorical will be analyzed by linear or mixed model regression models, and dichotomous variables by logistic regression models. Stratification factors utilized in the randomization will be used as covariates. Qualitative and exploratory methods will be used as required.

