## 7 METHODS

### 7.1 Method overview

This is a prospective multicenter randomized controlled trial. Screening for study subjects takes place among women with threatening premature birth in the antenatal and labor ward, with randomization taking place antenatally. The study population is 150 infants (75 infants in control and in intervention) born between gestational age 28+0 and 32+6 weeks at Karolinska University Hospital labour wards in Danderyd and Huddinge in Stockholm and at Stavanger Universityhospital in Norway. The intervention is skin-to-skin contact with either parent or with a surrogate chosen by them, the SSC should be uninterrupted during the first six hours of life, and as much as possible in the first 72 hours. Data will be collected during this time, and then during the period of admission, and continued until the infant reaches 24 months corrected age (described further below). Certain selected outcomes will be studied in subsamples of the 150 subjects, and for practical reasons some at only one site. Some families studied may later be transferred elsewhere in the country, data for these will continue to be collected as far as possible. There may also be certain exclusions due to language and interpreter problems that may influence data. Discussion on sample sizes for subsamples is ongoing.

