## **8 TRIAL SUBJECTS**

### **8.1 Inclusion criteria**

- Birth at gestational age between 28+0 and 32+6 weeks.
- Born in labor ward at study site.
- Consent from prospective parents, with interpreter if required.
- Parent or surrogate available to commence skin-to-skin contact in the first hour of life.

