### **8.2 Exclusion criteria**

- Born outside hospital
- Triplets or higher multiples
- Known congenital malformation requiring surgical management.
- Known congenital infection.
- Any other circumstance precluding subject from enrollment according to responsible clinician.

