### **8.3 Criteria for interruption and cessation**

The intervention will sometimes not be able to be initiated immediately and will at times require to be temporarily halted for events and procedures that cannot be done safely in SSC. This does not imply withdrawal from the study, as such situations are expected. Prospective parents will have consented to study participation with information about the importance of adhering to allocated place of care in the first six hours of life. Clinical staff will support such adherence. If parents demand otherwise, this may be accepted after individual assessment by the clinically responsible neonatologist as to safety of infant. Actual time in allocated place of care, as well as time in other place of care will be documented. Criteria for temporary interruption of SSC, with intention to continue straight after, will be:

- If the infant requires intubation
- If the infant requires umbilical catheters
- If infant despite adequate measures has hypothermia
- If infant despite support has repeated severe apnoea and bradycardia
- If infant requires any other intervention and this cannot be done safely in SSC, as assessed by ward staff and responsible neonatologist.

Should the parents of any study subject wish to withdraw from the study this will be accepted. Data collected up to that point will be analyzed unless the parents expressly wish otherwise. Clinical staff may also in consultation with research staff choose to terminate a subject's participation under particular circumstances.

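### The primary set labelled intention to treat drops randomised infants on eligibility criteria that can be settled after open allocation, so losses can differ by arm; adherence-based analyses would tend to favour skin-to-skin contact

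*Protocol*

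**What the plan says.** Section 11.2 describes the primary analysis as "intention to treat (ITT) on all subjects that met inclusion criteria without exclusion criteria and were randomized". For safety it takes a different set: "For safety measures the entire sample will be included". The efficacy set can therefore be smaller than the randomised sample.

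Two criteria matter most here:
- Section 8.1 requires "Parent or surrogate available to commence skin-to-skin contact in the first hour of life".
- Section 8.2 excludes for "Any other circumstance precluding subject from enrollment according to responsible clinician", with no time limit.

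On timing, section 7.1 speaks of screening women before delivery, "with randomization taking place antenatally". Section 7.2 sets the limit at one hour before birth. Section 8.6 allows allocation from six hours before birth to one hour after it. Section 8.7 says that allocation cannot be blinded.

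Section 11.2 adds two analyses: "Per protocol analysis will also be undertaken based on actual adherence to allocated place of care", and "The analysis will be done for the whole study population as well as those that received the intervention". Section 8.3 lists the reasons for temporarily interrupting skin-to-skin contact (SSC). They include intubation and "If infant despite support has repeated severe apnoea and bradycardia". The same section says that interruptions are expected and do not amount to withdrawal.

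**The concern.** Randomisation protects a comparison only if what happens after allocation does not decide who is counted. Here the set called intention to treat is filtered by eligibility. Part of that filter can be applied after allocation by staff who know the arm.

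First-hour availability is the clearest case. It can be confirmed only once the infant is born, and it has a practical consequence mainly where SSC has to start. An unavailable parent could be recorded as an eligibility failure in one arm and pass unnoticed in the other. The discretionary exclusion is open to the same problem if it is used late. Nothing in the protocol confines these judgements to facts known before randomisation or requires them to be made without sight of the arm.

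The adherence-based analyses raise a second issue. The primary score, SCRIP, is built from respiratory rate, oxygen saturation, respiratory support and pulse (section 6.1). Two of the reasons for interrupting SSC are cardiorespiratory events of the same kind. Section 14.2 adds that the smallest infants, and those needing longer stabilisation, may begin on the resuscitaire. If time off SSC removes an infant from an analysis, the infants removed will tend to be the unstable ones.

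**Working it through.** **Which criteria can be settled after allocation**

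| Criterion | When it can be settled |
|---|---|
| Gestational age at birth; birth in the study labour ward (8.1) | At birth, but an objective fact |
| Parent or surrogate available in the first hour (8.1) | After birth |
| Known malformation or known infection (8.2) | Reads as known at enrolment |
| Clinician's discretion (8.2) | Reads as an enrolment decision, but no cut-off is stated |

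Under sections 7.1 and 7.2 every infant is allocated before birth, so the first-hour criterion always follows allocation. Under section 8.6 it could be checked first only for infants allocated after birth.

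**Size: inputs**

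The protocol gives no figure for this, so there is none to reproduce. From section 7.1: 75 infants per arm. Two-sided 5% test, as in section 11.3. Assumed: no true effect, a stability score with SD 1, a fraction x of one arm dropped, and correlation ρ between being dropped and low stability.

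**Formulas**

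- Shift in the arm mean = ρ × φ(z) / (1 − x), where z is the normal quantile at x and φ the normal density.
- SE = √(1/75 + 1/n), where n is the number left in the reduced arm.
- False-positive rate = P(Z > 1.96 − r) + P(Z < −1.96 − r), with r = shift/SE.

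**4% dropped from one arm (3 of 75), ρ = 0.5**

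- Shift = 0.5 × 0.0862/0.96 = 0.045 SD.
- SE = √(1/75 + 1/72) = 0.165, so r = 0.27.
- False-positive rate ≈ 5.9%.

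**About 10% dropped (8 of 75, x = 0.107), ρ = 0.5**

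- Shift = 0.5 × 0.1839/0.893 = 0.103 SD.
- SE = √(1/75 + 1/67) = 0.168, so r = 0.61.
- False-positive rate ≈ 9.4%.

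**Simulation with a t-test (10,000 trials per row, same assumptions, ρ = 0.5)**

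| Who is dropped | Shift (SD, + favours SSC) | False-positive rate |
|---|---|---|
| 4% of SSC arm, less stable | +0.04 | 5.9% |
| 10% of SSC arm, less stable | +0.10 | 9.9% |
| 4% of control arm, less stable | −0.05 | 6.1% |
| 10% of control arm, less stable | −0.10 | 9.5% |
| 5% to 20% of both arms alike | about 0 | 5.4% to 6.2% |

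With ρ = 0, dropping 4% to 30% of one arm gives no bias and about 5%. The size and sign therefore depend on who is dropped and why.

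**Adherence-based sets**

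Suppose that interruptions did remove infants, and that 20% of the SSC arm (15 of 75) left. At ρ = 0.5 the formula gives 0.5 × 0.350 = +0.175 SD. The simulation gives +0.17 SD and 18% false positives; at ρ = 0.8 it gives +0.28 SD and 40%. The 20%, and the rule that an interruption removes an infant, are both assumptions.

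**The case against.** **Direction.** A reader might infer that the primary result is biased toward SSC. The documents do not support that. The criteria apply to both arms, nothing ties an unavailable parent to an unstable infant, and the table above gives zero or opposite bias under other patterns. The idea that failures would be noticed mainly in the SSC arm is reasonable, but it is an inference.

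**Which criteria.** A reader might also count known malformation, known infection and clinician discretion as criteria that only birth can settle. The wording of section 8.2 points to enrolment. That objection stands for malformation and infection. For discretion, what remains is the missing cut-off.

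**Rarity and size.** Either parent or a chosen surrogate satisfies the availability criterion, so failures may be few. Assuming that exactly the least stable infants of one arm are lost would roughly double the shifts, but nothing supports so extreme a case. The planned mixed model includes gestational age, birth weight and growth restriction, and may absorb part of any imbalance that the unadjusted calculation shows.

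**The other analyses.** They are additional, so they cannot alter the primary result. Section 8.3 treats interruptions as expected, section 11.2 does not say that an interrupted infant leaves the per-protocol set, and an adherence threshold may properly sit in an analysis plan that is not shown. Adherence also applies to control infants. To say that these analyses favour SSC by construction would assume a definition the protocol does not contain. What stands is a tendency.

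**Whole study population.** Section 11.2 also promises an analysis of the whole study population, which might mean no efficacy exclusions. If so, it conflicts with the definition given earlier in that section, and the text still needs correcting.

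**Conclusion.** The concern holds in limited form. The set called intention to treat is conditional on eligibility. At least one criterion is settled after birth, one is discretionary with no cut-off, and allocation is open and usually made before birth. As written, exclusions made with knowledge of the arm can enter the primary comparison.

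The direction is not fixed. Under assumed losses of 4% to 10% from one arm at correlation 0.5, the shift is about 0.04 to 0.10 SD and the false-positive rate about 6% to 10%. With equal loss in both arms there is almost no bias. The losses and the correlation are illustrations, not protocol figures.

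The adherence-based analyses would tend to favour SSC, because reasons for leaving SSC overlap with the components of SCRIP. How far depends on a per-protocol definition that the protocol does not give.

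**What to change.** 1. Define the primary set as every randomised infant, analysed in the allocated arm.
2. Allow exclusion only on facts fixed before randomisation or on objective birth facts (gestational age, place of birth). Have these judged without sight of the arm, and list them by arm.
3. Apply parent or surrogate availability and clinician discretion before randomisation only.
4. Reconcile the randomisation timing in sections 7.1, 7.2 and 8.6, since it decides which criteria can be checked before allocation.
5. Label the per-protocol analysis and the analysis of those who received the intervention as supportive. In the per-protocol set, do not count an interruption for a section 8.3 reason as non-adherence.
6. State what the whole study population means, so that it agrees with item 1.

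The cost is protocol wording and a small change to the analysis. The downside is that a few infants who could not receive SSC stay in and slightly dilute the estimated effect.

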### **8.6 Determination of allocation**

Randomization will be done by electronic means, close to the actual birth time but at earliest 6 hours before birth and latest one hour after birth.

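### Twins are eligible, but the linear and logistic models named in section 11.2 do not allow for pairing; twin allocation is unstated, and site and strata are not clearly in the primary model

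*Protocol*

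**What the plan says.** **Who is counted.** Protocol section 8.2 excludes "Triplets or higher multiples", so twins may enter. Section 7.1 counts infants: "The study population is 150 infants (75 infants in control and in intervention" arms. Section 11.3 also sizes the trial in infants.

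**How they are allocated.** Section 8.6 says "Randomization will be done by electronic means, close to the actual birth time". It names no strata and does not say whether co-twins receive one allocation or two. Section 7.1 describes the trial as multicentre.

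**Primary model (section 11.2).** "For the primary outcome a mixed model-regression analysis will be done to evaluate the effect of gestational age, birth order, single or multiple birth", followed by growth retardation, mode of birth, antenatal steroids and birth weight. No random effect is named. Site is not in the list. The next sentence gives the null hypothesis of no difference between the groups.

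**Secondary models (section 11.2).** "Secondary outcomes that are continuous or categorical will be analyzed by linear or mixed model regression models, and dichotomous variables by logistic regression models". The sentence that follows reads "Stratification factors utilized in the randomization will be used as covariates".

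**The concern.** Two babies from one pregnancy share gestational age, antenatal steroid exposure, parents and usually mode of birth, so their outcomes are likely to be correlated. Ordinary linear and logistic regression treat each row as independent. Fixed terms for birth order and multiplicity shift the mean for twins but leave the within-pair correlation in the residuals. The logistic sentence offers no mixed alternative, so binary outcomes such as sepsis and need for surfactant are assigned a model that does not fit paired data. The linear-or-mixed sentence leaves the choice open for the rest.

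The primary model has a related gap. The covariate sentence about strata stands in the secondary-outcome paragraph, and the primary model's own list has neither strata nor site. If strata were used in the randomisation and then left out of the primary analysis, precision that the design bought would be lost.

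At stake are the width of the confidence intervals, the true error rate of the tests and, for the primary outcome, some power.

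**Working it through.** The protocol states no figure for twins or clustering, so there is none to reproduce.

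**Inputs**
- N = 150 infants, 75 per arm (section 7.1); two-sided 0.05 (section 11.3).
- f, the share of infants who are twins: not given. Assumed 25%, range 15–35%.
- ρ, the intra-pair correlation: not given. Assumed 0.5, range 0.3–0.7.
- c, the share of twin pairs with both infants in one arm: not given. It is 1 if co-twins share an allocation, about 0.5 if each infant is randomised independently, and 0 if pairs are split.

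**Formula.** In a difference of two means with equal arms, a pair in the same arm adds covariance and a pair in opposite arms removes it. There are Nf/2 pairs, so the variance relative to independence is

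DE = 1 + f·ρ·(2c − 1).

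Effective N = 150/DE. The true error of a nominal 5% test that ignores pairing is 2·[1 − Φ(1.96/√DE)]. For a binary outcome this is an approximation, with ρ on the binary scale.

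**Results**

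| f, ρ | Co-twins share an arm: DE / effective N / true error | Randomised independently: DE / true error | Pairs split: DE / true error |
|---|---|---|---|
| 15%, 0.3 | 1.045 / 144 / 5.5% | 1.00 / 5.0% | 0.955 / 4.5% |
| 25%, 0.5 | 1.125 / 133 / 6.5% | 1.00 / 5.0% | 0.875 / 3.6% |
| 35%, 0.7 | 1.245 / 120 / 7.9% | 1.00 / 5.0% | 0.755 / 2.4% |

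For the middle row with a shared arm: DE = 1 + 0.25 × 0.5 = 1.125; 150/1.125 = 133; 1.96/√1.125 = 1.848; 2·[1 − Φ(1.848)] = 6.5%.

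**Simulation check.** A linear model with fixed terms for multiplicity and birth order was simulated at N = 150, with f = 20–40% and ρ = 0.3–0.7 (4,000–6,000 runs per setting). The error was 5.6–8.5% with co-twins in one arm, 4.6–5.6% with independent randomisation, and 2.4–4.4% with split pairs. The formula over the same range gives 5.7–8.3% (shared) and 2.1–4.3% (split). The two fixed terms therefore do not remove the problem.

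**Power.** With a shared arm, a comparison that had 90% power for 150 independent infants has Φ(3.24/√DE − 1.96): 89%, 86% and 83% down the rows of the table.

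**Strata left out of the primary model.** Suppose balanced strata explain a share R² of the outcome variance, assumed 5–20%. An unadjusted analysis reports a standard error too large by the factor 1/√(1 − R²), which is 1.03 to 1.12. The true error of its nominal 5% test is 2·[1 − Φ(1.96/√(1 − R²))], which is 4.4% to 2.8%. This acts in the opposite direction to shared-arm pairing.

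**The case against.** The strongest reply is that much of this is silence, and that random-effect structure is normally left to an analysis plan, which is not at hand. Several parts of that reply stand.

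- A reader might infer that the protocol treats twins as independent throughout. It does not say so. The primary analysis, and one option for the secondary ones, is a mixed model that could carry a family effect, repeated SCRIP scores or both.
- A reader might infer that the primary model certainly omits the strata. The strata sentence is not expressly limited to secondary outcomes, and nothing shows whether site is a stratum. If it is, that sentence could already cover it.
- A reader might infer that allocation is missing as the effect to be estimated. The null hypothesis in the next sentence implies the group comparison, though the wording is loose.
- A reader might infer that standard errors are too small. That requires co-twins to share an arm. Randomisation before birth suggests one allocation per pregnancy but does not prove it, and section 8.6 allows randomisation up to one hour after birth.
- A reader might infer that maternal questionnaires, cortisol and fMRI are counted twice for mothers of twins. No section says they are analysed per infant. Only the unit of analysis is unstated.

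The reply does not dispose of the point. The protocol is not silent on model class: it assigns logistic regression to dichotomous outcomes and permits plain linear regression for the others. How co-twins are allocated is a design matter that belongs in the protocol, whatever an analysis plan may contain.

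**Conclusion.** The point holds for the secondary linear and logistic models as named. For the primary model it holds as a lack of specification. The size is modest and its direction is not known. On the assumed 15–35% twins and correlation of 0.3–0.7, ignoring pairing gives a true error of about 5.5–7.9% if co-twins share an arm, about 5% under independent randomisation, and about 2.4–4.5% if pairs are split. Leaving prognostic strata out of the primary model would be conservative and would cost power. The documents do not show that standard errors in the primary analysis are wrong. The changes are worth making because they are cheap and remove the dependence on an unstated allocation rule.

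**What to change.** - **Section 8.6:** state the unit of randomisation for twins (one allocation per pregnancy, or separate allocations and by what rule), and name the stratification factors.
- **Section 11.2, primary model:** name a random effect for mother, with infants nested in mother and repeated SCRIP scores nested in infant. State that allocation is the effect of interest and that the randomisation strata and site enter as covariates.
- **Section 11.2, secondary models:** for infant-level outcomes, including those analysed by logistic regression, use the same mother-level effect, or GEE or cluster-robust errors by mother.
- **Mother-level outcomes:** state that they are analysed once per mother. If co-twins can be in different arms, also state how such a mother is assigned to a group.

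The cost is a few sentences and slightly more complex models. Intervals become slightly wider if co-twins share an arm: by a factor of √DE, about 1.02 to 1.12 on the assumptions above.
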